### Sample size

The sample size is 400 women with 80 to 120 women enrolled within any one county.

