### Analysis

Three *a priori* group contrasts will be used to test the primary hypotheses regarding intervention effects on the use of dental services (see Table 1 for a summary of the 4 study groups):

(1) Groups 1 and 2 (MI Prenatal) versus Groups 3 and 4 (HE Prenatal) will test the hypothesis that the MI intervention results in a greater frequency of utilization of dental care by the woman during pregnancy.

(2) Groups 1 and 3 (MI Postpartum) versus Groups 2 and 4 (HE Postpartum) tests the hypothesis that the MI intervention results in a greater frequency of utilization of preventive dental care by the children during the first 18 months of life.

(3) Group 1 (MI Prenatal and Postpartum) versus Group 3 (MI Postpartum only) will test the hypothesis combination of MI delivered during pregnancy and postpartum will result in a greater frequency of preventive dental care for children during the first 18 months of life.

A significance level of 0.016 was used in the sample size and power calculations for the primary hypotheses to take into account the three comparisons to be performed. The study will also provide some evidence for the effect of MI during pregnancy, without MI postpartum, on child utilization. However, the study is not powered to demonstrate this effect, which will likely be modest in the absence of intervention postpartum.

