### Missing data

Based on efforts to reduce attrition and missing data shown to be effective in our previous intervention work [20], and employed in this study, we expect to have an 80% retention rate of participation over the course of the study period. We will have even less missing data regarding dental utilization because we are able to obtain utilization data from the Medicaid database on all subjects, except those who explicitly refuse further participation in the study. In the case of non-ignorable non-response, a method based on augmented inverse probability of censoring weighted estimating equations will be used to perform a sensitivity analysis that examines how the estimated intervention effect on the primary outcome measure changes over a range of plausible values for the non-response mechanism [40].

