Additionally, it is hypothesized that outcomes will be mediated by a women’s readiness to change. We will test whether changes in readiness to change over the course of the intervention mediates the effects of MI on the outcome measures for the mother at three months post-partum and for the child by 18 months of age. First, the analyses for the primary hypotheses will be used to examine whether there is an effect of the MI intervention on mother’s outcomes at three months post-partum and child outcomes by 18 months of age. Second, to demonstrate the association between the intervention and readiness to change, we will construct regression models with readiness to change as the dependent variable (e.g., change between baseline and three months post-partum for the mother’s outcomes, and change between and/or three months postpartum and 9 or 18 postpartum for the child’s outcome) and intervention and the baseline value of readiness to change as independent variables. Third, to demonstrate the association between readiness to change and the outcome after adjusting for the intervention and to demonstrate the reduction of the intervention effect on the outcome after adjusting for readiness to change, we will construct regression models with both treatment and readiness to change as independent variables and the outcome measure as the dependent variable.

To formally test the mediation effect as described in the third step above, we will use a version of the Sobel test [41], which tests whether the indirect effect of intervention on the outcome through the mediator (defined as the product of the intervention to mediator path and the mediator to outcome path) is significantly different from zero. The mediation effect is referred to as the indirect effect of intervention because it reflects the intervention effect on the outcome through the mediating variable [42]. We will use the bootstrap method of Preacher and Hayes [43] to estimate the indirect effect and bias-corrected 95% confidence interval (CI) for each individual mediator and for all the mediators as a group, based on 1,000 bootstrap samples using a Statistical Package for the Social Sciences (SPSS®; SPSS Inc., Chicago, Illinois) macro (http://www.afhayes.com/spss-sas-and-mplus-macros-and-code.html).

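### The secondary mediation interval rests on 1,000 bootstrap resamples, which adds avoidable seed noise to borderline results; separately, its bias correction can make it mildly liberal when one path is null

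*Protocol article*

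**What the plan says.** Under Secondary aims, the protocol article sets out a stepwise mediation analysis. It looks for an MI effect on the outcome, then for an MI effect on readiness to change, and then fits both together. For the formal test it states: "we will use a version of the Sobel test [41], which tests whether the indirect effect of intervention on the outcome through the mediator" differs from zero. It then adds a bootstrap, whose stated purpose is this: "estimate the indirect effect and bias-corrected 95% confidence interval (CI) for each individual mediator and for all the mediators as a group". The same sentence fixes the number of resamples ("based on 1,000 bootstrap samples"), to be run in an SPSS macro.

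Both the type of interval and the number of resamples are therefore stated settings. The article gives no expected size for either path and no second interval as a check.

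Two other statements set the scale. The Sample size section says: "The sample size is 400 women with 80 to 120 women enrolled within any one county". The Missing data section says: "we expect to have an 80% retention rate of participation over the course of the study period". The mediators come from questionnaires, so the retention figure applies to them even though the utilization outcomes come from Medicaid claims.

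**The concern.** A 95% limit taken from 1,000 resamples rests on about 25 draws in each tail. The bias-corrected form also has to estimate its shift from the same draws. When the lower limit lies close to zero, the random seed can decide whether mediation is reported. That error belongs to the computing, not to the data, and more draws shrink it.

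A second question is whether the interval keeps its nominal 95%. The null that matters here is that a mediator such as readiness predicts dental use but MI moves it no more than health education does. This is plausible: the article lists Readiness Ladder status among the important predictors of utilization (Primary outcome analysis), and the comparator is an active one (Study treatments). If the interval excludes zero too often in that situation, the trial could credit a mediator with carrying an effect that it does not carry.

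**Working it through.** **Inputs from the article.** Table 1: 148 + 52 + 148 + 52 = 400 women. Retention 80%: 0.80 × 400 = 320 with mediator data. Prenatal contrast: 200 v 200, so 160 v 160 retained. Postpartum contrast: 296 v 104, so 0.80 × 296 = 236.8 and 0.80 × 104 = 83.2, taken as 237 v 83.

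**Assumed inputs.** MI-to-mediator path *a* from 0 to 0.39 SD; mediator-to-outcome path *b* from 0 to 0.6 log odds per SD; one continuous mediator; binary outcome with logistic regression.

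**The interval.** Let z0 = Φ⁻¹(share of bootstrap products below the estimate). The limits are the bootstrap percentiles at Φ(2·z0 ± 1.96). The percentile interval sets z0 = 0.

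**Step 1: Monte Carlo error of the limits.**
- Tail draws: √(0.025 × 0.975 / B). For B = 1,000 this is 0.0049, or 0.49 points on a 2.5% tail; for B = 10,000 it is 0.16 points.
- Estimating z0: 2 × [√(0.25/B) / φ(0)] × φ(1.96). For B = 1,000 this is 2 × (0.0158 / 0.399) × 0.0584 = 0.0046, or 0.46 points; for B = 10,000 it is 0.15 points.

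**Step 2: how often two seeds disagree on the same data (bias-corrected).** The first three rows are a large-sample check with true path z-values. The last is a trial-size simulation (1,000 datasets at B = 1,000; 250 at B = 10,000).

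| Scenario | 1,000 resamples | 10,000 resamples |
|---|---|---|
| z-values 0 and 3 | 1.8% | 0.6% |
| z-values 2 and 3 | 5.5% | 1.8% |
| z-values 3 and 3 | 4.5% | 1.1% |
| *a* = 0.25 SD, *b* = 0.3, about 320 women | 6.0% | 2.4% |

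The affected band is narrow. With estimated path z-values of 1.8 and 3.5, 60% of seeds call the result significant at 1,000 resamples and 91% at 10,000. With 2.0 and 3.5, over 99% of seeds agree at either count.

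**Step 3: coverage against the stated 95%.** The article shows no calculation behind the nominal figure, so it was checked by simulation: 2,004 datasets per scenario, 1,000 resamples, simulation SE about 0.5 points.

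| *a*, *b* | BC, 160 v 160 | BC, 237 v 83 | Percentile, 160 v 160 | Percentile, 237 v 83 |
|---|---|---|---|---|
| 0, 0 | 99.7% | 99.7% | 99.8% | 100.0% |
| 0, 0.14 | 98.2% | 98.3% | 99.2% | 99.0% |
| 0, 0.39 | 93.6% | 92.7% | 95.9% | 95.1% |
| 0, 0.6 | 94.4% | 93.3% | 95.6% | 94.4% |
| 0.14, 0.39 | 94.1% | 93.4% | 95.4% | 94.6% |
| 0.39, 0.14 | 93.7% | 93.2% | 94.8% | 94.4% |
| 0.25, 0.39 | 96.4% | 95.4% | 95.4% | 94.5% |
| 0.39, 0.39 | 96.4% | 95.4% | 95.7% | 95.0% |

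At *a* = 0 the indirect effect is zero, so false positives are 100% minus coverage. At *b* = 0.39 that is 6.4% and 7.3% for bias-corrected (BC) and 4.1% and 4.9% for percentile. A separate simulation (*b* = 0.4, about 45% using care) gave 6.4% and 7.6% against 4.6% and 5.0%. In the large-sample check, BC coverage ran from 91.8% (z-values 1 and 2) to 99.5% (0 and 0). With one path null the worst was 92.7% (0 and 4).

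**Step 4: power.** At *a* = 0.25, *b* = 0.39, BC has 64.4% and percentile 55.8% (160 v 160, a gap of 8.6 points); for 237 v 83, 53.2% and 46.3% (about 7 points). The separate simulation gave 55% and 44% (11 points). The largest gap in the large-sample check was 34.3% − 23.0% = 11.3 points.

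**The case against.** The strongest reply is that the interval does not stand alone. The same section first asks whether MI changes readiness. When it does not, that step should fail about 95% of the time at the 5% level, and a Sobel-type test is also named. If a mediation claim needs every step, the chance of a false one is held near or below 5%. This stands as a real mitigation. It is not complete, because the article does not say that the interval is read only after the earlier steps succeed, and an interval will be given for each mediator.

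The bias-corrected form is also a defensible choice. It buys power, at a cost of 1 to 3 points of coverage in some configurations. This stands too, and is why replacing it is not required. The seed is a detail that a condensed article may leave to the full protocol, so its absence is not part of the point.

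A reader might infer that the interval generally covers less than 95% at this trial's size, or that the 1,000 resamples cause the shortfall. Neither is supported. Coverage depends on the standardised path sizes, and the shortfall comes from the bias correction. Nor is it established that the 74:26 split makes the excess larger. The gap between 6.4% (3,000 datasets) and 7.6% (2,500 datasets) is 1.2 points with SE about 0.7, and the other simulation's gap (6.4% v 7.3%) is also within its error.

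**Conclusion.** The point holds as a minor one, in two separate parts.

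- **Resample count.** At 1,000 resamples about 2% to 6% of datasets change verdict between seeds, against about 2.5% or less at 10,000. Only borderline results are exposed, and 10,000 reduces the problem without abolishing it.
- **Bias correction.** When one path is null or weak and the other moderate, coverage is about 92% to 94%. With MI not moving a mediator that moderately predicts the outcome, false positives are roughly 6% to 8%. With both paths null they are under 1%, and with both clearly non-zero coverage is at or above 95%.

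The figures rest on assumed path sizes and on one continuous mediator, without county, counselor or baseline-readiness terms. They may differ for an ordinal Readiness Ladder or for several mediators taken as a group. Mediation is a secondary aim, so the three primary contrasts and the 0.016 level are untouched.

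**What to change.** In Secondary aims, raise the bootstrap count from 1,000 to at least 10,000 and record the seed. The seed makes the run reproducible; only the larger count reduces the Monte Carlo error. From the same resamples, report the percentile 95% interval beside the bias-corrected one as a prespecified sensitivity check, and state that mediation will be claimed with caution where one excludes zero and the other does not.

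The cost is computing time. Making the percentile interval the only one would bring false positives to about 4% to 5% in the main problem case (*a* = 0, *b* about 0.4) but lose about 7 to 12 points of nominal power, part of which is merely the excess error given back. That replacement is the sponsor's choice and is not needed to settle this point.

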## Discussion

The prevalence of Early Childhood Caries among disadvantaged North American populations ranges from 17-61% [44-47] and is as high as 87% among preschoolers living in rural communities [48-51]. Marked regional disparities in the prevalence of Early Childhood Caries have been documented with up to 73% of children in rural regions experiencing dental caries, compared with 51% in urban areas [52]. Early Childhood Caries has major impacts on quality of life, causing pain, eating and sleeping problems [53-56]. Understanding how health disparities are created, exacerbated or mitigated, and reproduced across generations is essential to eliminating differences [57].

Clinicians’ attempts to educate parents about the importance of children’s oral health have had mixed success and the two studies using Motivational Interviewing [16,20,21] obtained different results. The results of this trial should provide guidance for implementing brief cognitive interventions that may be more effective. In designing this trial, we purposely chose a community setting. We did this to increase buy-in and increase generalizability. We also used a carefully-scripted approach to both the MI and HE interventions. We did this because the interventionists had little or no previous training or experience with oral health of pregnant women or young children.

This trial is unique in that the primary outcome is drawn from Medicaid insurance claims rather than self-report or a clinical examination. The choice to utilize administrative data should minimize missing outcome data due to the loss to follow-up that often plagues longitudinal studies in low-income populations.

## Abbreviations

MI: Motivational interviewing; HE: Health education.
